**Fig. 1 Fig1:**
[figure not shown]
Study flow chart. Sequence of steps from eligibility assessment to data analysis in both settings

### Primary outcomes

The feasibility of a prospective RCT on MBT-CD will be estimated based on the acceptability of the intervention and scientific assessments by the participating adolescents as well as the estimated organizational resources needed.

Acceptability of the intervention will be evaluated based on quantitative and qualitative data:
Recruitment rates, and consent ratesCompletion ratesDrop-out rates and reasonsTreatment duration in months and number of sessionsOral evaluation of the intervention by the patients assessed via standardized questions

Acceptability of the scientific assessments will be evaluated based on quantitative and qualitative data:
Adherence rates, missing dataPreference of online or paper-pencil assessmentsOral evaluation of the assessments by the patients

Resources needed by the organization will be determined regarding:
Scientific personnelRecruitment networks, clinical cooperationsMBT trainings and supervision

### Secondary outcomes

#### CD symptom severity

Fulfillment of CD criteria assessed with the Mini-International Neuropsychiatric Interview for Children and Adolescents (M.I.N.I. KID) [31] and the Structured Clinical Interview for DSM-IV Axis II Disorders (SCID-II) [32]Levels of aggression assessed with the Reactive–Proactive-Aggression Questionnaire (RPQ) [33]Antisocial behavior measured with the Subtypes of Antisocial Behavior Questionnaire (STAB) [34]

#### Mentalizing

Mentalizing assessed with the Reflective Functioning Questionnaire (RFQ) [35]The Brief Reflective Functioning Interview (BRFI) [36]The Movie for the Assessment of Social Cognition (MASC) [37]

### Additional assessments

#### Sociodemographic data and childhood experiences

AgeGenderAttended type of schoolChildhood and adolescent experiences of neglect and abuse in the family context will be measured with the Childhood Experience of Care and Abuse Questionnaire (CECA-Q) [38]

#### Global and personality functioning

Global functioning assessed with the Global Assessment of Functioning Scale (GAF) [39], the Clinical Global Impression – Severity Index (CGI-SI) [40], and the General psychological symptom severity is measured with the Symptom-Checklist-90-Revised (SCL-90-R) [41]Personality functioning assessed with the Levels of Personality Functioning – Questionnaire for Adolescence (LoPF-Q 12-18) [42]Emotion regulation assessed with the Emotion Regulation Questionnaire (ERQ) [43]Personality Pathology assessed with the Dimensional Assessment of Personality Pathology – Basic Questionnaire (DAPP-BQ) [44]Psychopathy-like traits will be assessed with the Youth Psychopathic Traits Inventory (YPI) [45]

#### Experience of patient-therapist and other relationships

Adolescents’ experience of the therapy working alliance assessed with the Working Alliance Inventory-Short Revised (WAI-SR) [45]Attachment anxiety and avoidance assessed with the Experiences in Close Relationships Scale-Revised Child-Version (ECR-RC) [46]Experience of parental behavior assessed with the Zürcher Brief Questionnaire for the Assessment of Parental Behaviors (Zürcher Kurzfragebogen zum Erziehungsverhalten, ZKE) [47]

#### Parental mentalizing, stress, and experience of relationships

Mentalizing assessed with the Reflective Functioning Questionnaire (RFQ [35])Parental Stress assessed with the Stress Index for Parents of Adolescents (SIPA) [48]Attachment anxiety and avoidance assessed with the Experiences in Close Relationships Scale-Revised (ECR-R) [49]

### Cost-effectiveness

Cost-effectiveness assessed with an adapted version of the European version of the client sociodemographic and service receipt inventory (CSSRI-EU) [50]

### Participants

Adolescents with CD or ODD according to the Diagnostic and Statistical Manual for Mental Disorders (DSM) [1] aged between 11 and 18 years are included in the study. Participants are recruited at the participating centers as well as with leaflets (two separate versions for adolescents and parents), which are distributed through multipliers and institutions (e.g., child and youth welfare services, schools, police stations, probation officers). Prospective participants or caretakers can contact the treatment centers via phone (number provided on the leaflet) to indicate their interest, ask questions, and be screened for eligibility criteria through a standardized checklist assessing rule-breaking and defiant behavior. Participants receive a total of 50€ for taking part in the scientific assessments.

### Eligibility criteria

Adolescents are included if their main diagnosis is CD or ODD. The latter is a precursor or milder form of CD, with a pattern of angry, irritable mood, argumentative/defiant behavior, or vindictiveness [1]. The pattern needs to last over the course of at least 6 months and needs to be exhibited in interaction with at least one individual, who is not a sibling. Moreover, the pattern needs to be associated with distress in social contexts or negative consequences for important areas of functioning [33]. Adolescents with CD or ODD are only included if they are between 11 and 18 years of age and both, adolescents and their parents provide written informed consent (forms based on templates of the European General Data Protection Regulation, GDPR [51];). Adolescents are excluded if they have committed sexual offenses, show acute psychotic symptoms, suffer from early or early-onset schizophrenia, have neurological impairments or intelligence severely below average (IQ < 60) as measured with the Culture Fair Intelligence Test (CFT) [52], are non-German-speaking or have other clinical contraindication for outpatient psychotherapy (e.g., acute suicidality).

Concomitant therapies or interventions including hospital stays are permitted, but will be assessed via the CSSRI-EU [50] and reported with the study results.

### Intervention

MBT-CD is a CD-specific adaptation of MBT [53]. The primary goal of MBT-CD is the recovery of the mentalizing capacity in close relationships and along with this, a reduction of symptoms, especially aggressive and antisocial behavior. The treatment duration is 6 to 12 months and consists of up to 30 weekly individual sessions with the adolescent and up to 10 monthly family sessions. At the beginning of the individual sessions, the adolescent’s mentalizing capacity will be diagnosed (diagnostic phase). Before the 30 individual and 10 family sessions, adolescents and their families attend two psycho-educational workshops. After the end of treatment, 3 booster sessions follow. When indicated, youth welfare services are involved.

The psycho-educational workshop (MBT-CD Introductory Workshop, MBT-CD-I) aims to familiarize the adolescent and their family with the mentalizing concept, educate about CD, the MBT-CD treatment goals, and to strengthen therapy adherence. MBT-CD-I focuses on the topics of mentalizing (i.e., what is mentalizing, failures of mentalizing), emotions (i.e., basic emotions, emotion recognition), attachment and identity, and conflicts and boundaries.

After completing MBT-CD-I, adolescents start with their individual sessions. At the beginning of the individual sessions, therapy goals are developed using motivational interviewing and the therapist writes a case formulation about the adolescent’s main mentalizing difficulties, both in collaboration with the adolescent. Moreover, prior to working on improving mentalizing abilities, risk behavior is assessed and a risk emergency plan is developed if necessary. Then, throughout the main treatment phase, MBT-CD focuses on the therapeutic relationship to improve the adolescent’s mentalizing. With the therapist holding the adolescent’s mind in their mind, non-mentalized emotions (rather than cognitions) and their representations can be explored with regard to core problem behavior. MBT-CD focuses on the development of a basic understanding of interpersonal situations, emotions, and failures of mentalizing that trigger antisocial and aggressive behavior. The monthly family sessions (MBT-CD-F) aim to create a mentalizing environment by exploring dysfunctional mentalizing within the family system [54]: With the therapist’s help, family members describe non-mentalizing interactions in detail (noticing and naming), mentalize the interactions (mentalize the moment), formulate potentially dysfunctional family interaction patterns, and consider possible alternatives (generalize and consider change). Reciprocal understanding between therapist and all family members is continuously monitored (checking). This way, MBT-CD-F targets problematic family interactions by practicing mentalizing within relevant interpersonal context and hence enhancing the family’s self-regulatory strategies [54]. At the end of therapy, three booster sessions will follow to stabilize treatment effect (see Fig. 2).

**Fig. 2 Fig2:**
[figure not shown]
The process of MBT-CD in both settings

### Treatment adherence

MBT-CD will be delivered by therapists who have undergone psychotherapy training, have the legal right to treat patients under supervision, and who have participated in a 4-day MBT-CD training conducted by the first author (ST). Videos of each session will be obtained. Supervision will be provided in biweekly sessions. During supervision, case material (including therapy videos) is reviewed with regard to the therapist’s understanding of MBT theory and use of MBT interventions. Per therapist, six videos of one of their MBT-CD therapies will be randomly chosen to be rated for therapist adherence and competence with the MBT Adherence and Competence Scale [55].

### Statistical analysis

All analyses will be performed according to the intention to treat principle. Analyses on quantitative data will be conducted using the statistical software SPSS (IBM, Version 25). Sociodemographic data and data of the scientific assessments at baseline (T1, see Table 1) will be used to characterize the sample. Primary outcome variables (recruitment rates, drop-out rates, and missing data of adolescents as well as parents) will be descriptively analyzed. The distribution of treatment duration (in months and number of sessions) will be analyzed to infer the optimal dose of treatment and necessary flexibility in treatment dose and duration. Scientific personnel costs will be estimated based on timely effort (hours needed per month, total number of months). Secondary outcome variables will be investigated using multilevel modeling. Content analysis will be used to investigate qualitative data (drop-out reasons, oral evaluations of MBT-CD, and the scientific assessments). As additional subgroup analysis, binomial logistic regression will be conducted modeled after Jorgensen and colleagues [56], who identified low RF, but not clinical or sociodemographic variables to predict drop-out of MBT group treatment in adolescents with borderline personality disorder. Data entry will be double checked and range checks for data values will be conducted. Pseudonymized data will be anonymized as soon as possible. Anonymized data will be stored in Heidelberg according to the European GDPR [51] and deleted 10 years after study completion.

**Table 1 Tab1:** Overview of the scientific assessments and time points in both settings

		Measure	T1^a^	T2^b^	T3^c^	T4^d^
Adolescent		WAI-SR		X	X	
		STAB	X	X	X	X
		RPQ	X	X	X	X
		YPI	X			
		CFT-2	X			
		LoPF-Q 12-18	X		X	X
		MASC	X		X	
		RFQ-8	X		X	X
		ECR-RC	X		X	X
		ERQ	X		X	X
		ZKE	X		X	
		BRFI	X		X	
		CECA-Q	X			
		M.I.N.I KID	X		X	
		SCID-II	X		X	
		CGI-SI	X		X	
		SCL-90-R	X		X	
		DAPP-BQ	X			
		GAF	X		X	
		CSSRI-EU	X	X	X	X
Parent		SIPA	X		X	X
		RFQ-8	X		X	X
		WAI-SR		X	X	
		ECR-R	X		X	

*WAI-SR* Working Alliance Inventory-Short Revised, *STAB* Subtypes of Antisocial Behavior Questionnaire, *RPQ* Reactive–Proactive-Aggression Questionnaire, *YPI* Youth Psychopathy Traits Inventory, *CFT-2* Cultural-Fair-Test 2, *LoPF-Q 12-18* Levels of Personality Functioning – Questionnaire for Adolescents, *MASC* Movie for the Assessment of Social Cognition, *RFQ* Reflective Functioning Questionnaire, *ECR-RC* Experiences in Close Relationships Scale-Revised, *ERQ* Emotion Regulation Questionnaire, *ZKE* Zürcher Brief Questionnaire for the Assessment of Parental Behaviors, *BRFI* Brief Reflective Functioning Interview, *CECA-Q* Childhood Experience of Care and Abuse Questionnaire, *M.I.N.I. KID* Mini-International Neuropsychiatric Interview for children and adolescents; *SCID-II* Structured clinical interview for DSM-IV axis II personality disorders, *CGI-SI* Clinical Global Impressions – Severity Index, *SCL-90-R* Symptom-Checklist-90-Revised, *DAPP-BQ* Dimensional Assessment of Personality Pathology – Basic Questionnaire, *GAF* Global assessment of functioning, *CSSRI-EU* European version of the client sociodemographic and service receipt inventory, *SIPA* Stress Index for Parents of Adolescents

^a^Beginning of treatment

^b^3 months after the beginning of treatment

^c^End of treatment

^d^3 months after the end of treatment

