So far, meta-analyses have shown that a number of interventions are effective in reducing CD symptoms [12, 13]. Among these, cognitive-behavioral therapy, social skills training, parent training, and multi-systemic therapy are regarded as evidence-based treatments [12, 14]. They differ in their involvement of parents or peers, but their focus on CD symptom management is common to all. However, effect sizes are small, conduct problems oftentimes persist and it remains unclear which treatment works best for whom and why [12]. Moreover, drop-out rates of around 20% [12] and low motivation to seek treatment in the first place render the effective and sustainable treatment of CD pathology difficult. Importantly, interventions are so far lacking a comprehensive etiological understanding of CD, which may entail the failing of targeting relevant mechanisms contributing to the development and maintaining of CD symptoms. In line with this notion, authors call for specification of interventions to target specific individual or subgroup deficits [11, 12] and base them on knowledge about underlying patho-mechanisms [11].

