## Methods/design

### Aims

The primary aim of the feasibility and pilot study is to estimate the feasibility of an RCT on MBT-CD based on acceptability of the intervention (indicated by recruitment rates into treatment, drop-out rates and completer rates, and adolescents’ oral evaluation), acceptability of the scientific assessments by the patients and family (indicated by adherence rates to the scientific assessments, and adolescents’ oral evaluation), and organizational resources needed to conduct an RCT in an outpatient only and a combined outpatient and inpatient setting in the future. The secondary aim is the examination of CD-symptom severity over time, the course of aggressive and antisocial behavior, and changes in mentalizing. The primary aim of the future RCT will be to determine the effectiveness of MBT-CD in terms of CD symptom severity, levels of aggression, and antisocial behavior as well as an appropriate comparison group. The secondary aim of the RCT will be to investigate the change in a proposed patho-mechanism (i.e., mentalizing) and general symptom severity through MBT-CD.

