### Design

The study is a feasibility and pilot trial to form the basis for a future, prospective RCT. The study is carried out at two treatment centers in Heidelberg (Institute for Psychosocial Prevention) and Mainz (Pediatric and Adolescent Psychiatry Mainz), Germany. Adolescent participants receive MBT-CD over the course of 6 to 12 months. Adolescents and their parents are asked to take part in study assessments every 3 months during treatment and 3 months after the end of treatment (for an overview of study flow see Fig. 1). The design is adaptive in that both, intervention and scientific assessments can be changed in the course of the study, if, e.g., drop-out rates and reasons indicate necessary adjustments for successful study continuation. Originally, this feasibility trial was designed as a single-blinded RCT to test the effectiveness of MBT-CD compared to treatment as usual (TAU) delivered as an outpatient treatment at the Clinic of Child and Adolescent Psychiatry at the University-Hospital Heidelberg. This comparison group was chosen as it is in line with the routine health care treatment for adolescents with CD [30]. Due to recruitment problems identified in yearly interim recruitment analyses, the design was changed into a non-randomized single group feasibility and pilot trial. This decision was made in consensus with the study funders (Dietmar-Hopp-foundation and Heidehof foundation) upon fulfilling the study termination criterion of recruiting less than 20% of the a priori estimated overall sample size of 102 adolescents within 1 year (to detect a medium effect and considering 25% drop-out).

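### The spread of months and sessions received can show which dose is deliverable and acceptable, but not, as the plan says, which dose is optimal

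*Protocol article*

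**What the plan says.** The Statistical analysis section of the protocol article gives the distribution of treatment duration, counted in months and in sessions, two purposes: it "will be analyzed to infer the optimal dose of treatment and necessary flexibility in treatment dose and duration". Four other places bear on this.

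- **Design:** after recruitment problems in the planned RCT, "the design was changed into a non-randomized single group feasibility and pilot trial".
- **Intervention:** treatment lasts 6 to 12 months and "consists of up to 30 weekly individual sessions with the adolescent and up to 10 monthly family sessions".
- **Primary outcomes:** duration and number of sessions are listed as indicators of how acceptable the intervention is.
- **Aims:** the clinical question is left for later: "The primary aim of the future RCT will be to determine the effectiveness of MBT-CD".

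**The concern.** An optimal dose is the dose with the best result, so finding it requires results at different doses. The analysis named here looks only at how much treatment patients received. A typical or common dose could then be reported as the best one, although nothing in the analysis compares doses.

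This matters because the study exists to inform an RCT, and the length and intensity of treatment are design choices for that RCT. A dose labelled optimal would carry more authority into that choice than the data can give it.

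**Working it through.** The plan gives no figure for this point, so there is none to reproduce. The check is what the named analysis can identify.

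**1. What enters the analysis.** Months and sessions per patient. Symptom severity and mentalizing are secondary outcomes, with multilevel modeling given as their own method in the same section. The sentence on dose does not draw on them.

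**2. How dose arises.** There is a single group without assigned dose levels (Design), so the dose received is whatever patient, family and therapist arrive at.

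**3. What bounds it.** The manual sets 6 to 12 months and ceilings of 30 individual and 10 family sessions (Intervention). The distribution therefore partly reflects what was offered. It is silent on anything above the ceilings.

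**4. What can be read from it.**

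| Question | Answerable from the distribution? |
|---|---|
| How much treatment was delivered? | Yes |
| How far does the dose vary, and so how much flexibility is needed? | Yes |
| Is the dose acceptable? | Yes, as one indicator among those listed |
| Which dose gives the best outcome? | No |

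**5. Illustration with assumed values (none from the protocol).** Let severity *S* be standard normal, sessions = 18 − 3*S* + 6*e* with *e* standard normal, rounded and limited to 1–30, and outcome = *f*(sessions) − 0.5*S* + noise (standard normal, higher is better). In a simulation of 200,000 patients the session quartiles were 13, 18 and 23. The same set of sessions was combined with three dose-response curves *f*:

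| Assumed truth | Best dose | Median sessions received |
|---|---|---|
| Flat | None | 18 |
| Peak at 10 sessions | 10 | 18 |
| Rising by 1/30 per session | 30 (the cap) | 18 |

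The distribution is the same in every row while the best dose differs, so the distribution cannot tell the rows apart.

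**6. Would adding outcomes rescue the claim?** Not readily, because dose is not assigned. In the same illustration, severity affects both sessions and outcome. Ignoring rounding and limits, a simple slope of outcome on sessions is biased by (0.5 × 3)/(3² + 6²) = 1.5/45 = 0.033 per session. The simulation gave 0.035 where the true slope was 0, and 0.068 where it was 1/30 = 0.033. The actual size and direction in this trial are unknown. The protocol itself also permits concomitant therapies (Eligibility criteria) and changes to the intervention during the study (Design), both of which would blur a link between dose and outcome further.

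**The case against.** The strongest reply is that *optimal* here means practicable. Primary outcomes places duration and sessions under acceptability. The sentence stands between the descriptive feasibility analyses and the estimate of personnel costs, and effectiveness is left to the RCT. A target dose and the variation allowed around it are also naturally two feasibility quantities, so naming flexibility separately does not prove that an efficacy claim was meant. The protocol further collects drop-out reasons and oral evaluations to help adapt the treatment.

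Much of this stands: the authors may well have meant the practicable dose. But the sentence does not say so, and it presents the result as an inference about the optimal dose. If the milder meaning was intended, the rewording below states it at no loss. Drop-out reasons and oral evaluations can inform acceptability and adaptation, but they do not identify a best dose either.

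A second reply is that a condensed article may leave a dose-outcome analysis to a fuller document. That is fair, and its absence is not held against the plan. The point concerns a purpose the article does state and the basis it names for it.

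**Conclusion.** The sentence is wrong as written, with minor consequence. From this distribution, in a single group without assigned doses and within limits set by the manual, the study can describe the dose delivered, its acceptability and the flexibility needed. It cannot infer an optimal dose. This follows from the stated design and does not depend on the assumed values in the illustration. The one interpretive step is taking *optimal* in its ordinary sense of giving the best result.

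Three stronger readings are tempting, and the documents do not support them:

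- **That the future RCT will be built on a wrong dose.** The article does not commit the RCT to the inferred dose.
- **That the feasibility results are compromised.** No recruitment, completion or drop-out rate depends on this sentence, and no sample size does.
- **That drop-out will distort the typical dose by a known amount.** The article names no summary statistic for the distribution and does not say how drop-outs enter it, so no size can be given. A condensed article may leave out such detail.

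**What to change.** In Statistical analysis, replace the purpose of inferring an optimal dose with *to describe the dose delivered and its feasibility and acceptability*. Keep the second purpose, on necessary flexibility, unchanged. Draw no conclusion on optimal dose from this study; where the text can no longer be changed, apply the same limit when reporting results.

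The cost is one sentence, with no new data and no new analysis. The downside is that one promised conclusion is withdrawn.

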## Discussion

This protocol outlines the process of a feasibility and pilot study on MBT-CD in adolescents with CD or ODD. So far, treatments focusing mainly on symptom management remain unsatisfactory in treating patho-mechanisms possibly contributing to CD. Consequently, CD symptoms often persist [12], leading to unfavorable long-term prognoses and, together with insufficient understanding of CD etiology, a pessimism in the treatment of CD [57]. Thus, researchers call for improving CD treatment, e.g., through an integration of knowledge about the etiology and pathological pathways (e.g., [11]). As dysfunctional mentalizing has been linked to the development of CD (cf. [18, 22, 23]), targeting specific mentalizing deficits in this patient group presents a promising approach for a more successful and sustainable treatment of CD and CD (relapse) prevention. However, so far, there are no treatments focusing specifically on mentalizing in adolescents with CD. To fill this gap and aim at a more long-term positive effect on aggressive, norm-violating, and rule-breaking behavior, the authors have developed MBT for CD. Combining individual and family sessions, MBT-CD aims at improving mentalizing in adolescents with CD or ODD and their families within 6 months to 1 year of treatment. In line with the CONSORT statement [58], we aim at investigating the feasibility of an RCT in this patient group in the first step before conducting an RCT investigating its effectiveness in a second step. Several characteristics might render the conduct of an RCT in this patient group especially difficult: e.g., adolescents with CD oftentimes do not express a wish for help or display help-seeking behavior; specific fears may concern losing credibility in their peer group and portraying themselves as “weak.” Moreover, drop-out rates of adolescents with CD are usually high [12], possibly inter alia due to disorganized and avoidant attachment strategies [59]. For this reason, the study design is adaptive, which helps to address CD-specific reservations to the intervention or to the scientific assessments during treatment. Moreover, the consultation of adolescents’ oral evaluations at the end of treatment in addition to the analysis of quantitative data will further help to develop and adapt the treatment in close collaboration with the adolescents. Ultimately, the goal is to provide a treatment, which engages adolescents with CD or ODD and helps fostering the ability to create and maintain healthy relationships and understand triggers of one’s own destructive behavior. As such, MBT-CD is aimed to increase the adolescents’ chances of leading a healthy and satisfying life and along with this, of economically contributing to society.

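### Drop-out regression: with the few drop-outs likely here, a joint ordinary logistic model would overstate odds ratios, and a non-significant predictor would say little about absence of association

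*Protocol article*

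**What the plan says.** The Statistical analysis section of the protocol article adds one model for drop-out: "As additional subgroup analysis, binomial logistic regression will be conducted modeled after" a cited study. It reports that this study "identified low RF, but not clinical or sociodemographic variables to predict drop-out of MBT group treatment" in adolescents with borderline personality disorder. The article gives no predictor list, does not say whether predictors enter jointly, and attaches no caution about small numbers.

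The figures that bear on the number of drop-outs lie elsewhere:
- Design: the randomized design was abandoned on "recruiting less than 20% of the a priori estimated overall sample size of 102 adolescents within 1 year". The 102 was set "to detect a medium effect and considering 25% drop-out".
- Background and rationale: existing treatments have "drop-out rates of around 20" percent.
- Discussion: "drop-out rates of adolescents with CD are usually high", without a number.

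No target or achieved sample size is given for the present single-group study.

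**The concern.** The named method is ordinary binomial logistic regression, and the template examined three families of predictors. The information in such a model is governed by the smaller outcome group, here the drop-outs, and the recruitment history suggests few of them. Maximum likelihood with few events per predictor pushes odds ratios away from 1 and gives very wide intervals. It also has little power, so a non-significant clinical or sociodemographic variable would look like a replication of the cited result while carrying almost no evidence.

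Drop-out is among the primary feasibility outcomes, and the study exists to plan an RCT. An inflated mentalizing odds ratio, or a null taken at face value, could misdirect retention planning for that trial.

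The label is also wrong. Regressing drop-out on baseline variables in the whole sample is a predictor analysis, not a subgroup analysis.

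**Working it through.** **The plan's own figures.** The termination threshold is 0.20 × 102 = 20.4, so at most 20 adolescents were recruited in the year concerned. The 102 itself cannot be confirmed or refuted, because alpha, sidedness and power are not stated. It belongs to the superseded design and serves here only as a generous upper case.

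**Inputs.** Drop-out of 20% (Background and rationale) and 25% (Design). N = 20 to 60 is an assumption. Three or five jointly entered predictors is also an assumption.

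**Expected drop-outs and best-case precision.** With p the drop-out proportion:
- expected drop-outs = N × p
- for one standardized predictor, SE(log OR) ≈ 1/√(N p (1 − p))
- the 95% limits lie a factor exp(1.96 × SE) either side of the estimate
- the odds ratio detectable with 80% power is exp((1.96 + 0.8416) × SE)

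For N = 20 and p = 0.20, N p (1 − p) = 3.2, SE = 0.559 and the detectable odds ratio is exp(2.8016 × 0.559) = 4.8.

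| N | Drop-out | Expected drop-outs (95% binomial range) | Per predictor, 3 / 5 predictors | CI factor | Detectable OR per SD |
|---|---|---|---|---|---|
| 20 | 20% | 4 (1-8) | 1.3 / 0.8 | 2.99 | 4.8 |
| 20 | 25% | 5 (2-9) | 1.7 / 1.0 | 2.75 | 4.3 |
| 40 | 20% | 8 (3-13) | 2.7 / 1.6 | 2.17 | 3.0 |
| 40 | 25% | 10 (5-16) | 3.3 / 2.0 | 2.05 | 2.8 |
| 60 | 20% | 12 (6-18) | 4.0 / 2.4 | 1.88 | 2.5 |
| 60 | 25% | 15 (9-22) | 5.0 / 3.0 | 1.79 | 2.3 |
| 102 | 25% | 25.5 (17-34) | 8.5 / 5.1 | 1.57 | 1.9 |

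If drop-out were 40% (assumed) at N = 40, there would be 0.40 × 40 = 16 events.

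The approximation is optimistic in small samples. At N = 20 it gives 24-27% power for an odds ratio of 2 per SD; simulated fits gave below 8%.

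**Simulated ordinary fits.** True odds ratio 1.5 per SD for one predictor, standard normal predictors, 600 data sets per setting. Where two values are given, the simulation was run twice.
- N = 20, 20% drop-out, five predictors: 30-33% of fits separated; 95% of fitted odds ratios between 0.06 and 367 (second run 0.07 and 192); power under 1%.
- N = 30, 25%, five predictors: range 0.36 to 24 (second run 0.45 to 15); power 9-10%; separation about 1%.
- N = 40, 25%, one predictor: range 0.69 to 4.2 (second run 0.69 to 3.8); power 14-15%.
- N = 40, 40%, five predictors: power 17%.
- N = 60, 25%, five predictors: range 0.74 to 4.2; power 21%.
- N = 102, three to five predictors: power 40-44%.

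In a separate simulation with a true odds ratio of 2, N = 40 and 25% drop-out, separation or non-convergence stayed under 1% even with five predictors.

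**Bias, ordinary against Firth.** The true log odds ratio is 0.405, with five predictors and 25% drop-out.

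| N | Mean log OR, ordinary | Mean log OR, Firth |
|---|---|---|
| 30 | 1.60 | 0.43 |
| 40 | 0.72 | 0.41 |
| 60 | 0.50 | 0.42 |

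At N = 60 the ordinary mean corresponds to exp(0.50) = 1.65 against a true 1.5. Root mean squared error was lower with Firth in every setting tried, including N = 40 with 40% drop-out. The ordinary means at N = 30 and 40 depend on how near-separated fits are counted. Leaving out fits that do not converge brings them closer to the truth, but they stay above it, while Firth stays close to it.

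**The case against.** The strongest reply is that both decisive inputs are assumed. The figure of at most 20 is a one-year count under a randomized design, not a total. First enrollment was on 19.01.2017, the protocol version is dated 20.08.2020, Mainz was still recruiting, and randomization had been dropped. An assumed 15 per year over 3.5 years would give 15 × 3.5 = 52.5, more than 50 patients; an assumed 40% drop-out among 50 would give 20 events. This stands. A reader might infer that the model is bound to rest on some 4 to 10 drop-outs, but the documents do not support that as a fixed number.

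A reader might also infer that the plan copies a full multivariable model, or that the missing predictor list is itself a fault. The article says only that the regression follows the cited study, and an article commonly leaves the list to a fuller document. So the point is conditional on joint entry. An unseen list could reduce the number of predictors but not add drop-outs.

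Three further inferences go too far:
- That the fits will often separate. This is so only near N = 20; at N = 40 and above the defect is bias and imprecision.
- That the investigators will declare clinical and sociodemographic factors irrelevant. The wording "who identified low RF, but not clinical or sociodemographic variables to predict drop-out of MBT group treatment" describes the cited study's result and is not a planned conclusion.
- That null results would be meaningless. An interval still excludes very large effects; what it cannot do is support absence of a moderate one.

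Finally, the analysis is neither a primary nor a secondary outcome. Retention lessons will come mainly from descriptive drop-out rates and content analysis of reasons. That limits the consequence. Restricting the model to one predictor also does not make the question answerable: power remains about 15% at N = 40.

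**Conclusion.** The concern holds in conditional form. If N is about 20 to 60 and 20-25% drop out, about 4 to 15 drop-outs are expected. If several predictors enter an ordinary logistic model together, that is roughly 1 to 5 events per predictor. The odds ratios would be biased away from 1 and too imprecise to interpret, and non-significance would be uninformative about absence of association.

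The power part does not hinge on the assumed N: even at the abandoned target of 102, a true odds ratio of 1.5 per SD would be missed more often than found. The bias is clear at N = 30 to 40 and modest at N = 60. The subgroup label is a misnomer on the text alone.

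This is a worthwhile correction to an additional analysis and does not threaten the study's primary aim.

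**What to change.** Amend the Statistical analysis section as follows:
- Fit a Firth-penalized logistic regression of drop-out on one baseline mentalizing score, named before the data are analyzed.
- Report the odds ratio with a profile penalized-likelihood 95% interval and make no significance claim.
- Show clinical and sociodemographic baseline values descriptively, by drop-out status.
- Call it an exploratory predictor analysis in place of a subgroup analysis.
- State the number of drop-outs beside the result, and that absence of association will not be concluded.

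No change to data collection is needed. The price is that no adjusted estimates will be available, and that a routine outside base SPSS may be needed. Penalization removes most of the bias and copes with separation; it does not supply power, which is why the interval, and not a test, should carry the result.
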